### Follow-up

Currently, funding is assured for at least two years of follow-up. For an extension of the follow-up, additional funding is required. We will contact patients half-yearly by telephone to ascertain outcomes and to update the patients' profile using the baseline patient history form and we will send them the questionnaires. After two years we will additionally measure lung function and exercise capacity again. We will ask patients about exacerbations during the follow-up interviews. In addition, the Swiss GPs will be asked to complete a form each time an exacerbation occurs and fax it to the study center. The Dutch investigators will review the patient charts for possible exacerbations. Thus, this combination of means to document exacerbations will minimize the chance of missing exacerbations requiring medical treatment, Also, for each patient, an independent and blinded adjudication committee (2 experienced pulmonologists and 1 GP) will check all clinical evidence from all available documents to judge whether the doctor or hospital visits were due to an exacerbation and to distinguish these from other events mimicking exacerbations such as heart failure.

To take into account changes in the patients' profile over time, we will interview patients during follow-up about dyspnea, cough, physical activity, smoking status and treatment as described above. Based on experience in earlier studies, these follow-up interviews will require about 25 minutes.

### Statistical analysis – prediction model

In choosing an approach to the statistical analysis, the use of the risk index in practice should be kept firmly in mind. The goal is prediction of the course of illness as expressed in health-related quality of life, risk of exacerbation and mortality. In principle, the CRQ has four domains (dyspnea, fatigue, emotional function, and mastery) and domain-specific predictions probably will trigger different therapeutic actions. So, potentially, seven different prediction models can be built: 4 on the CRQ domains, one for the overall CRQ score, one for exacerbation risk, and one for mortality, respectively. These models are likely to have at least some predictors in common. We envision that a practitioner will collect all predictors and receive a pattern of 7 predictions to discuss with the patient and base the therapy on. The added value of information whose collection requires more time (sit-to-stand test, questionnaires) will be systematically assessed. Obviously, the different endpoints require the use of different regression techniques: linear regression (CRQ), Cox regression for recurrent events (exacerbations) and Cox or logistic regression for mortality.

In clinical terms we envision the use of a prediction model in the following situations. First, in patients who visit the practice and are first diagnosed as having COPD. And second, in patients known to have COPD, who are identified through the electronic patient charts for a scheduled follow up visit. Our model will not be optimally suitable for use at unscheduled visits, triggered perhaps by exacerbations due to our exclusion criterion on current exacerbations.

Issues important in constructing multivariable models depend on the purpose of the multivariable model (correcting for confounding in studying causal effects, exploratory analyses that try to identify independent risk factors, or prediction models). Even with the purpose in mind, there seems to be consensus that there is no consensus on how one should build multivariable models [32-34]. Here we will restrict to issues important in constructing prediction models. In particular, the issue of variable selection is contentious. Very often, subject matter knowledge is not of much help, since that has already been incorporated into the questionnaire development and the measurement of other (e.g. blood-based) determinants. Such questionnaires most often contain more items than a realistic model may tolerate. We favor parsimonious models because most clinicians have little time. Even data reduction techniques such as principal component analysis applied to many predictors, as proposed by Harrell [33], although facilitating efficient model fitting, still forces physicians to collect a lot of data. Usually there is no time to do that, although (in the future) there may increasingly be exceptions where part of the information may be collected from electronic patient charts or in the waiting room through an internet connection or from home prior to the actual visit. Most experts think that univariable screening of predictors should not be performed and we will avoid that.

Missing values in limited amounts and if scattered throughout different predictors may be dealt with by multiple imputation although it may require additional software programming to perform for example bootstrapped variable selection in more than one imputed data set and elegantly integrate the results from each imputed data set into a single model. By contrast, many missing data on just one or a few tests may indicate that such data will end up missing in practice too, so imputation and incorporation of such a test in a prediction rule seems unwise.

Royston and Sauerbrei emphasize the importance of modeling continuous predictors correctly, avoiding unnecessary categorization They argue that multivariable fractional polynomials may be seen as a flexible and convenient compromise between ultra-flexible but potentially unstable local influence models, such as (smoothing) splines and relatively inflexible global influence models, such as for example conventional polynomials [34]. We think that they argue their case convincingly and will explore multivariable fractional polynomials for our continuous predictor candidates such as age, exercise capacity test results and blood values.

The biggest issue of contention seems to be the one of variable selection. There is the choice between full models (which, as stated above, we think are impractical due to physicians' time restraints), backward elimination, shrinkage, lasso (least absolute shrinkage and selection operator) or least angle regression (LAR) and finally, one we think has much potential, the garotte [34-36]. The garotte is a shrinkage approach in which the degree of shrinkage is reduced as the predictor's regression coefficient gets larger. This is attractive since, according to Copas, large coefficients do not need (much) shrinkage. Lasso and general shrinkage may shrink large coefficients too much. A drawback of the garotte is that it starts with a full model which may be too large to fit. We expect to be able to explore the garotte if we succeed in programming it. The final model may still be subjected to enhanced bootstrap procedure to estimate over-optimism. This is usually expressed as the difference between areas under the curve or Brier scores. We will explore any over-optimism in the predicted values and their corresponding confidence intervals.

In much of the literature on prediction of cardiovascular disease, ongoing treatments in observational cohorts are not (explicitly) accounted for. This seems to be incorrect because it is easy to envision that the prognosis of a patient with high blood pressure while on antihypertensive treatment differ from a patient with high blood pressure without any treatment. For example in COPD, the prognosis of a patient with a low MRC score while on bronchodilators can differ from the prognosis of a patient with the same MRC score without bronchodilators. In ICECOLD ERIC we collect data on treatment (changes) and intend to use them in the models where necessary.

We will have several options to validate our prediction model. For example, the Dutch cohort could be the derivation set and the Swiss cohort the validation set or vice versa. One of other possibilities is that half of each cohort could be used as derivation set and the other half as validation set. Or, we can even combine all data to derive the model and test the model via bootstrap. At the time of writing, we have not decided which route we will follow. At the time we need to make that decision, we will try to find the best solution at that moment according to the statistical literature.

Discrimination of the model(s) will be visualized in high resolution histograms and summarized as 5^th^, 10^th^, 25^th ^50^th^, 75^th^, 90^th^, and 95^th ^centiles of these, Brier score and the area under the receiver operating characteristics curve (ROC) with 95% confidence intervals (overall discrimination)[37]. Using the regression coefficients of the independent diagnostic indicators, an easy to use, multivariable diagnostic rule (clinical index) will be derived, consisting of relevant tests and their diagnostic values [38]. Calibration will be assessed using Hosmer Lemeshow tests and visualized using calibration plots (observed versus expected (or rather, model-based) probabilities).

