### Sample size

The number of covariables that we will consider for the regression analysis is roughly 20, and using the rule that at least ten times as many patients are needed than covariables considered, we will need at least 200 patients per population.

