## Discussion

Management of COPD is challenging due to the various treatment options and the heterogeneous character of the disease. The actual (as opposed to ideal) assessment and treatment choices today are quite similar for all COPD patients and are often based on too few disease characteristics. This often leads to undertreatment of patients with severe COPD and overtreatment of patients with mild COPD. An example of overtreatment is the widely prescribed inhaled corticosteroids in mild patients. Results from recent studies suggest that GPs may not have methods available to sufficiently consider severity of disease for treatment decisions [3-11].

In preventive cardiovascular care, treatment decisions are based on the cardiovascular risk profile of the individual patient in primary care. Based on the most important predictors, patients fall into a specific risk profile. These profiles are formally coupled with treatment effects and costs considerations. Based on these components, treatment recommendations may be made. We believe that this so called risk index-guided treatment for specific patient profiles may well be applicable to COPD too.

The aim of this study to develop and validate a practical COPD disease risk index for the primary care will individualise and improve COPD management. Assessment of disease severity should not focus solely on lung function. An increasing body of evidence shows that additional information should be ascertained that better reflects disease severity than lung function [2,12-15].

We expect that after this study, the disease risk index will be ready for use in primary care. It will divide COPD-patients into specific risk profiles (low, medium and high risk) for each of the outcomes; COPD-specific health-related quality of life (domain-specific), exacerbation risk and mortality. In a second step we will incorporate treatment advices into the model by using data mainly from pertinent RCTs and meta-analyses. Ways to incorporate treatment advices into the prediction model may be challenging and are currently being explored by our team. In the development process of the cardiovascular risk model, the relative risk (RR) was treated as constant across all risk profiles.

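### For mortality and exacerbations the only formal calibration measure named is the Hosmer-Lemeshow test, which under assumed event rates misses most moderate miscalibration at about 200 validation patients

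*Protocol article*

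**What the plan says.** Under Statistical analysis – prediction model, the protocol article states: "Calibration will be assessed using Hosmer Lemeshow tests and visualized using calibration plots", the plots setting observed against model-based probabilities. In the same paragraph a 95% confidence interval is promised for the ROC area, as a measure of discrimination. No calibration slope, intercept, observed/expected ratio or calibration interval is named, and neither is a significance level, a number of risk groups or a pass rule.

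The event models are to be "Cox regression for recurrent events (exacerbations) and Cox or logistic regression for mortality".

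The validation route is left open. Options include that "the Dutch cohort could be the derivation set and the Swiss cohort the validation set or vice versa", that "half of each cohort could be used as derivation set and the other half as validation set", or that all data are pooled and tested by bootstrap. Sample size states that "we will need at least 200 patients per population".

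On use of the index, the Discussion says: "It will divide COPD-patients into specific risk profiles (low, medium and high risk) for each of the outcomes".

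**The concern.** The null hypothesis of the Hosmer-Lemeshow test is perfect calibration. The only favourable result it can give is a failure to reject, and that comes more easily with fewer patients and events. Its p-value depends on the grouping and shows neither the direction nor the size of an error. It also needs a yes/no outcome at a fixed time, which a recurrent-event Cox model does not supply directly.

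Absolute calibration matters here because patients are to be sorted into risk profiles, and later linked to treatment advice, by their predicted risks. An index whose predictions are too extreme, or shifted up or down, puts patients in the wrong profile even if it ranks them well. The planned size comes from a count of covariables and was not chosen with calibration in mind.

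**Working it through.** **The plan's own figure.** Sample size gives two inputs: "The number of covariables that we will consider for the regression analysis is roughly 20", and "at least ten times as many patients are needed than covariables considered". 10 × 20 = 200, so the stated minimum reproduces. The rule counts patients, not events.

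**Validation size at that minimum.** One country's cohort: 200. Half of each cohort: 0.5 × 200 + 0.5 × 200 = 200. Pooled data: 200 + 200 = 400.

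**Assumptions (not in the article).** Yes/no outcome at a fixed horizon; true risk logit(p) = a + s·z with z standard normal; s = 0.8 or 1.0 (AUC about 0.70–0.75); a solved to give event rates of 5%, 10%, 25% or 40%. The lower two rates are meant to resemble mortality and the upper two exacerbations. Nothing is refitted in the validation data.

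**Test.** X² = Σ (O_g − E_g)² / [E_g(1 − E_g/n_g)] over 10 risk groups, rejecting above the 95% point of chi-square with 10 df.

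**Errors examined.**
- Too extreme (slope 0.7): predicted logit = a + (s/0.7)·z.
- Odds 1.5 times too high: predicted logit = a + ln 1.5 + s·z.

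For comparison, the last column gives how often the 95% CI of the calibration intercept excludes zero for the second error. Each cell shows s = 0.8 / s = 1.0, from 10,000 simulated validation sets.

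| n | Event rate | Test rejects: no error | Test rejects: slope 0.7 | Test rejects: odds ×1.5 | Intercept CI: odds ×1.5 |
|---|---|---|---|---|---|
| 200 | 5% | 9 / 9% | 14 / 21% | 2 / 2% | 19 / 19% |
| 200 | 10% | 6 / 7% | 17 / 23% | 3 / 3% | 37 / 38% |
| 200 | 25% | 5 / 5% | 25 / 35% | 20 / 19% | 67 / 65% |
| 200 | 40% | 5 / 5% | 28 / 38% | 36 / 33% | 76 / 73% |
| 400 | 5% | 7 / 8% | 19 / 26% | 2 / 3% | 41 / 39% |
| 400 | 10% | 6 / 6% | 27 / 42% | 13 / 11% | 69 / 66% |
| 400 | 25% | 5 / 5% | 43 / 59% | 53 / 51% | 93 / 92% |
| 400 | 40% | 5 / 5% | 48 / 61% | 72 / 69% | 97 / 96% |

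**Missed at n = 200.** Slope 0.7: 100 − 38 = 62% to 100 − 14 = 86%. Odds ×1.5: 100 − 36 = 64% to 100 − 2 = 98%. Shorter independent runs gave 64–87% and 65–99%.

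**Missed at n = 400.** Slope 0.7: 39–81%. Odds ×1.5: 28–98%. Pooled bootstrap data hold less independent information than 400 fresh patients, so these figures are, if anything, favourable to the test.

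**Where the test does work.** At n = 200, AUC 0.70 and event rates of 30–50%, it detects an observed/expected ratio of 1.5 in 77–97% of sets, a ratio of 0.67 in 88–100%, and a slope of 0.5 in 84–87%. These are larger errors. At a 30% event rate, a ratio of 0.67 means a mean prediction of 0.30/0.67 = 0.45, with odds 0.81 against 0.43, about 1.9 times too high.

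**Limits of the comparison.**
- The slope scenario keeps mean predicted risk near the truth; matching it exactly gives 61–75% missed at n = 200. If a slope of 0.7 came with no such re-centring, rare events would be grossly under-predicted, and the test would detect that in 85–87% of sets at event rates of 5–10%.
- For predicted odds one third too low at a 5% event rate, the intercept interval detects no more than the test does (25% against 31%). The test's false-alarm rate there is about 9%.

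**Width of the alternative at n = 200.** The standard error of the slope, when the true slope is 0.7, is 0.19–0.23 at 10% events and 0.13–0.17 at 25–40%. Multiplied by 1.96, that is about ±0.37 to ±0.45 and ±0.25 to ±0.33. For well-calibrated predictions, divide the standard errors by 0.7: about ±0.53 to ±0.64 and ±0.36 to ±0.48.

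**The case against.** Several points on the other side stand.

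- The article sets no pass rule. A reader might infer that a non-significant test will be taken as proof of good calibration. That is a common way to read the test, but the article does not say it.
- Calibration is not left to the test alone. The same sentence plans observed-versus-predicted plots, which can show direction and size. They carry no stated interval, so at 200 patients a plot cannot by itself separate error from noise.
- Over-optimism is addressed elsewhere in the section: shrinkage methods are considered, an enhanced bootstrap may be applied, and over-optimism in predicted values is to be explored. The Brier score also responds to calibration. None of these is a calibration estimate with an interval.
- The validation size is not fixed at 200. That figure is a minimum, pooling would give about 400, and other cohorts may be added.
- Predictions are for one and two years, so a yes/no outcome can be defined for exacerbations. The test therefore needs adapting there; it is not impossible.
- Mortality and exacerbations are secondary outcomes. The primary outcome, the CRQ score, is modelled by linear regression and is not affected by this point.

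It can also be said that a condensed article leaves calibration detail to a fuller plan. That would answer a complaint about silence. Here the article names a specific method, and that method suits the purpose poorly.

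**Conclusion.** The concern holds in limited form. For mortality and exacerbations, the one formal calibration measure named cannot establish agreement, does not size the error, and at about 200 validation patients misses moderate miscalibration most of the time: roughly 62–87% for a slope of 0.7 and 64–99% for predicted odds 1.5 times too high. These figures depend on assumed event rates of 5–40%, AUC of about 0.70–0.75, ten groups, a 5% level and mean predictions near the truth in the slope case.

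The tempting stronger claim, that the test would pass almost any bad model, is not supported. Large errors in a common outcome are usually detected at 200 patients, and at 400 power is better, though still limited for moderate errors, especially for rare events. The article also does not commit its authors to relying on the p-value alone. The change is worth making because it is cheap and the index is meant to classify patients by absolute risk.

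**What to change.** Revise the calibration sentence under Statistical analysis – prediction model, for mortality and exacerbations:

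- Keep the calibration plots, smoothed and with a confidence band.
- Make the formal assessment calibration-in-the-large (intercept or observed/expected ratio) and calibration slope, each with a 95% confidence interval, at one and two years.
- For Cox models, use observed risk at the horizon, or expected against observed event counts for recurrent exacerbations.
- If the pooled bootstrap route is chosen, report optimism-corrected values; in the data used to fit a logistic model by maximum likelihood, slope and intercept are 1 and 0 by construction.
- If the Hosmer-Lemeshow test is still reported, state that a non-significant result is not evidence of good calibration.

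The cost is one or two sentences and a little more analysis work, with no new patients or data. The drawback is candour: at 200 patients the slope interval is about ±0.3 to ±0.45 when the true slope is 0.7 and events are 10–40%, and wider for well-calibrated predictions or rarer events. The authors may have to report calibration as uncertain.

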### Outcomes

The primary outcome, for which the risk index will be developed, will be COPD-specific health-related quality of life as measured by the Chronic Respiratory Questionnaire (CRQ). COPD-specific health-related quality of life is one of the main outcomes used in prognostic COPD research whether observational or interventional [11-13]. Secondary outcomes will include COPD exacerbations requiring medical treatment and mortality.

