#### Questionnaires

• COPD-specific health-related quality of life: we will use the widely used and validated Chronic Respiratory Questionnaire (CRQ) in a Dutch and German version [21,22]. The 20 questions of the CRQ provide summary scores for four domains that are deemed important to COPD patients (dyspnea, fatigue, emotional function, and mastery). Patients answer each question on a seven-point scale to express the degree of disability from 1 (maximum impairment) to 7 (no impairment). The total score and score per domain can be calculated by using the mean value ranging from 1 to 7. We will use the self-administered version that takes 5–10 minutes to complete. A change of 0.5 in CRQ domain scores represents the minimal important difference [23].

• Feeling thermometer: the Feeling thermometer is a validated visual analogue scale presented as a thermometer with 100 marked intervals [24-26]. The worst (dead = 0) and the best (perfect health = 100) health states are defined anchors and facilitate comparisons between individuals and groups. We will ask patients to reflect in their score how they have felt in the last seven days.

• Self-efficacy instrument: self-efficacy is the patient's belief in his or her skills to manage the illness. It is associated with medication compliance and might be a prognostic factor. We will use a short COPD-specific instrument to measure the patient's self-efficacy. It contains 3 questions about the management of their illness on a five-point scale from 1 (not confident) to 5 (very confident).

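### The four named performance measures need a binary event or a predicted probability, but the primary outcome (CRQ, 5 of 7 models) is a score fitted by linear regression and no CRQ event is defined

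*Protocol article*

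**What the plan says.** All references are to the protocol article.

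- **Outcomes:** the primary outcome, for which the index is to be built, "will be COPD-specific health-related quality of life as measured by the Chronic Respiratory Questionnaire (CRQ").
- **Questionnaires:** on scoring, "The total score and score per domain can be calculated by using the mean value ranging from 1 to 7". The same section gives 0.5 as the minimal important difference for a CRQ domain score. It is not used there or elsewhere to define an event.
- **Statistical analysis – prediction model**, on the type of model: "linear regression (CRQ), Cox regression for recurrent events (exacerbations) and Cox or logistic regression for mortality". The section counts seven possible models: four CRQ domains, overall CRQ, exacerbation risk and mortality.
- **Same section**, on discrimination: histograms of the predictions, their 5th to 95th centiles, and "Brier score and the area under the receiver operating characteristics curve (ROC) with 95% confidence intervals (overall discrimination").
- **Same section**, on calibration: "Calibration will be assessed using Hosmer Lemeshow tests and visualized using calibration plots (observed versus expected (or rather, model-based) probabilities").
- **Same section**, on over-optimism after an enhanced bootstrap: "This is usually expressed as the difference between areas under the curve or Brier scores". The authors then say they will explore over-optimism in the predicted values and their confidence intervals, without naming a measure.
- **Discussion**, on the finished index: "It will divide COPD-patients into specific risk profiles (low, medium and high risk) for each of the outcomes", with domain-specific quality of life listed among those outcomes.

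**The concern.** The article recognises that its endpoints need different regression techniques, but it does not carry that distinction into performance assessment. One set of measures is given for the models in general, and the four specific ones (ROC area, Brier score, Hosmer-Lemeshow, probability calibration plot) belong to event outcomes. The primary outcome is a score.

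The stated aim is to develop and validate an index. If the plan is followed as written, nothing named tells the reader how far predicted CRQ lies from observed CRQ, or whether predictions are systematically too high or too low. An analyst who wants to use the named measures for CRQ must first create an event. Since none is specified, the cut-off could be chosen after the data are seen, and the reported discrimination would depend on it. The low, medium and high risk profiles promised for quality of life have the same gap: no CRQ event stands behind the word risk.

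**Working it through.** **1. How many models are affected.** The article's own count is 4 (domains) + 1 (overall CRQ) + 1 (exacerbations) + 1 (mortality) = 7, which reproduces its figure. The linear CRQ models are 4 + 1 = 5 of 7, and they include every primary-outcome model.

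**2. What each named measure needs, against what a linear CRQ model gives.** The model output is a predicted score ŷ on the 1–7 scale, and the observation is a score y.

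| Named measure | Needs | Computable from (y, ŷ) without an event definition? |
|---|---|---|
| ROC area | event / no event for each patient | No |
| Brier score | 0/1 outcome and predicted probability | No |
| Hosmer-Lemeshow | observed and expected event counts in groups | No |
| Calibration plot as worded | observed and model-based probabilities | No |
| Histograms and centiles | predictions only | Yes, but y is not used |
| Over-optimism in predicted values | no measure named | Cannot be judged |

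So 0 of the 4 specific measures can be computed for CRQ as the plan stands.

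**3. Why histograms and centiles do not fill the gap.** An illustrative simulation was run with 200,000 draws. Its inputs are assumptions, not figures from the article: CRQ mean 4.5, SD 1.2, true R-squared 0.4, scores truncated to 1–7.

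- Correct predictions: 5th, 50th and 95th centiles 3.25, 4.50 and 5.74, so a 5–95 width of 5.74 − 3.25 = 2.49. Mean squared error 0.833, root √0.833 = 0.91 points.
- The same predictions all shifted up by 0.5, which is one minimal important difference: centiles 3.75, 5.00 and 6.24, width 6.24 − 3.75 = 2.49. Mean squared error 1.093, root √1.093 = 1.05 points.

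The spread is identical, while every prediction has been moved by 0.5 points and the error has grown. The increase of 1.093 − 0.833 = 0.260 is close to 0.5² = 0.25; the small remainder comes from truncation and sampling.

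**4. What happens if CRQ is dichotomised at an unspecified cut-off.** Same simulation, same model, event defined as CRQ at or above the cut-off:

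| Cut-off | 3 | 3.5 | 4 | 4.5 | 5 | 5.5 | 6 |
|---|---|---|---|---|---|---|---|
| Share at or above | 0.894 | 0.798 | 0.660 | 0.499 | 0.337 | 0.201 | 0.105 |
| AUC | 0.835 | 0.814 | 0.799 | 0.795 | 0.800 | 0.816 | 0.837 |

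One fixed model yields an AUC between 0.795 and 0.837 depending only on the cut-off. The range is modest and specific to the assumed inputs. It shows that the reported figure would depend on a choice the article does not make; it does not estimate what the study would find.

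**The case against.** The strongest reply is that this is a condensed article which openly defers several analysis decisions, and that measures for each outcome commonly sit in a statistical analysis plan that is not shown. Nothing in the article forbids reporting R-squared or prediction error, and design, data collection and choice of model are untouched. All of that is fair, and it limits the weight of the point. It does not remove it, because the article is not silent: it names its measures for the models in general, and those do not fit the model it names for the primary outcome.

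It can also be said that the Brier score has a continuous counterpart, mean squared error. That is true, but the article does not say it is meant, and its calibration wording refers to probabilities.

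A reader might infer more than the text supports:

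- **That every stated performance tool is unusable for CRQ.** The histograms and centiles can be drawn, and over-optimism in predicted values could be examined. The limit is that the first ignores observed scores and the second names no measure.
- **That over-optimism is defined by AUC or Brier differences.** The article says only that this is the usual expression. What the authors commit to concerns predicted values.
- **That dichotomising CRQ would contradict the article's own case against categorising.** That argument is about continuous predictors and says nothing about outcomes.
- **That the measures are inapplicable to exacerbations and mortality too.** Cox models can give event probabilities at a fixed horizon, and AUC and Brier score have versions for these. The article leaves the adaptation unstated, which is a smaller matter.
- **That Hosmer-Lemeshow must fail for mortality through lack of deaths.** The article gives no death count, no number of groups and no settled validation route, so this cannot be shown from it.
- **That the primary model cannot be validated, or only by post hoc dichotomisation.** Continuous-outcome measures are available, and an event probability can be derived from the linear model with a threshold fixed in advance.

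**Conclusion.** The point holds in a limited form. For the five CRQ models out of seven, which include every primary-outcome model, none of the four specific measures named can be computed without an event definition, and the article gives none. The tools that can be applied either do not compare prediction with observation or carry no named measure. This is a mismatch between a stated method and the stated primary model, and it should be settled before the follow-up data are analysed. It does not undermine the design, the data or the regression approach.

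The conclusion follows from the article's text alone. The simulated values illustrate the consequence and rest on the assumed mean, SD and R-squared.

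**What to change.** In Statistical analysis – prediction model, replace the single list of measures with one assigned by outcome.

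- **CRQ (four domains and overall):** R-squared; root mean squared prediction error in CRQ points, read against the 0.5 minimal important difference; and a plot of observed against predicted score with calibration intercept and slope. Correct each for optimism. The article gives the 0.5 for domain scores, so the reference for the overall score should be stated.
- **CRQ risk profile, if wanted:** prespecify the event, for example a decline of 0.5 or more from baseline, and keep the linear fit. Derive the probability from it: with baseline score b, predicted score ŷ and residual SD s, P(decline ≥ 0.5) = Φ((b − 0.5 − ŷ)/s) if residuals are close to normal, or use the empirical residual distribution. Apply AUC and Brier score to that probability.
- **Mortality and exacerbations:** keep Brier score, ROC area and probability calibration for these, with fixed-horizon, censoring-aware versions wherever Cox regression is used.

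The cost is revised wording and a little more analysis with standard software. No new data are needed.
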